### Data and safety monitoring

Adverse events are collected at every study visit and the site investigator rates their relationship to the medication. Serious adverse events are defined by the Therapeutics Goods Administration [45]. If serious or unexpected adverse events occur during the trial, they will be reviewed by the principal investigator and the trial team and be reported within the specified time to the lead hospital ethics review committee and to the data and safety monitoring board (DSMB), which comprises members independent of the research study and funding body. The DSMB will meet regularly to provide oversight and monitoring to ensure participants’ safety and the trial’s validity and integrity. The DSMB can request that the trial be terminated by the principal investigator in the event of safety concerns. Data will be double entered and source verification (data auditing) undertaken by a separate researcher upon the completion of the trial. Participants will be assigned a code and their information will be de-identified in password-protected documents.

### Primary outcome

The primary outcome is alcohol consumption expressed as self-reported number of HDDs (defined as at least four drinks for women and at least five drinks for men) per week. Any conflicting information will be validated by collateral reports and measurements of biological markers of alcohol consumption (phosphatidylethanol).

### Secondary outcomes

We will examine the time to lapse (any alcohol), time to relapse to heavy drinking, percentage number of days abstinent and the number of standard drinks per drinking day. We will also compare topiramate versus naltrexone on adverse events and BMI, tobacco use, levels of anxiety and depression (Depression, Anxiety and Stress Scale), cravings (Penn Alcohol Craving Scale), alcohol-dependence severity (Alcohol Dependence Scale), markers of liver injury (liver function tests) and sleep disturbances (Insomnia Severity Index and Pittsburgh Sleep Quality Index). We will explore the degree to which these clinical characteristics moderate treatment response and the mechanisms underlying these phenomena. We will also examine daily alcohol expectancies, drinking levels and the interaction of these factors with medication and genotype as in previous work [46].

### Genotyping

Genotyping of rs2832407 and rs1799971 will be performed rapidly (i.e. between the first and second visits) in the Department of Medical Genomics, Royal Prince Alfred Hospital, a recognised NATA-RCPA certified DNA genetic testing laboratory within NSW Health Pathology. DNA from whole blood will be isolated using a QIAcube automated extraction instrument (Qiagen). Genotyping for the SNPs rs2832407 in *GRIK1* and rs1799971 in *OPRM1* will be performed using TaqMan® SNP Genotyping Assays (Life Technologies). A polymerase chain reaction analysis will be performed using the following parameters: 60 °C for 30 s (data collection), 95 °C for 10 min, followed by 40 cycles of 95 °C for 15 s and 60 °C for 1 min (data collection), and finally 60 °C for 30 s (data collection). Genotypes will be read using the TaqMan Genotyping Software (v3.1) (Applied Biosystems). Any remaining whole blood will be stored for potential use in future studies.

### Sample size calculations

Power is considered for a two-sided test at α = 0.05 and a within-subject correlation of 0.35–0.40 for repeated measures. For the primary aim, the naltrexone versus topiramate analysis (grouped by time), we considered power for the comparison of the topiramate and naltrexone groups to have a small-to-moderate effect size, Cohen’s *d* = 0.33, at week 7 that will persist through week 12 based on Baltieri et al. [12]. Therefore, we have more than 80% power to detect a small effect size with our recruiting aim of *N* = 180 (*N* = 90 in each group). For the secondary aim, analysis of the moderating effect of *GRIK1*, we consider just the topiramate-treated patients in Kranzler et al. [17] in which the CC versus A carrier groups were separated at week 6 by a moderate effect size. Therefore, we have more than 80% power to detect a moderate effect size with *N* = 90 (as per above). The frequency of the rs2832407 C allele in individuals of European descent is approximately 60–65%, with 41–43% C allele homozygotes [15]. Our sample size calculations, thus, account for a prevalence of approximately 42% of the responsive CC genotype. The moderating effect of *OPRM1* is an exploratory aim given that: (i) there have been several investigations of the moderating role of this SNP on naltrexone in alcohol patients and (ii) the prevalence of Asp40 carriers is 15–25% and potential under-sampling will, thus, reduce the power to test the effect.

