### Statistical analysis

All available data from participants who took at least one dose of medication will be used, following the intention-to-treat principle. The primary outcome measure is frequency of HDDs (at least five standard drinks per day for men and at least four for women), which is a sensitive clinically relevant measure for alcohol trials [47]. Secondary outcomes (in addition to those listed above) will include number of abstinent days and average drinks per day. The two medication groups (naltrexone versus topiramate) will first be compared on weekly HDDs using mixed effects models followed by an analysis of secondary outcomes. Additional covariates will be included in the sensitivity analyses. Contrasts will also examine the final 6 weeks of the treatment period. Categorical variables will be compared using a chi-squared test. The medication by genotype groups will be compared using mixed models with fixed effects as intervention group (topiramate or naltrexone) and genotype (rs2832407*CC versus A carrier) as a moderating variable. The topiramate medication group will also be separately analysed with genotype as the fixed effect (CC versus A carrier). As with all alcohol treatment studies, we anticipate some participant dropout and intermittent missing data. Participants will be followed irrespective of whether they continue to receive treatment. Mixed effects models make use of all available responses under an assumption of ignorable missingness. The impact of missing data on the primary outcome measure will be explored by employing multiple imputation techniques and sensitivity analyses will be conducted to measure the effect of missing data on reported outcomes.

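### The topiramate-only CC versus A-carrier comparison, on which the GRIK1 aim is powered, is not randomised and has no planned ancestry adjustment, so part of any difference could be ancestry

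*Protocol article*

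**What the plan says.** All references are to the protocol article.

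- **Sample size calculations.** The GRIK1 aim is sized on topiramate-treated patients only. The basis is an earlier trial in which "CC versus A carrier groups were separated at week 6 by a moderate effect size", and the conclusion is that "we have more than 80% power to detect a moderate effect size with *N* = 90". The genotype frequency comes from one ancestry group: "The frequency of the rs2832407 C allele in individuals of European descent is approximately 60–65%, with 41–43% C allele homozygotes". The calculations are then said to "account for a prevalence of approximately 42% of the responsive CC genotype".
- **Inclusion and exclusion criteria; Patient recruitment.** No criterion concerns ancestry or ethnicity. Recruitment is through several Sydney hospitals, general practitioners, newspapers and websites.
- **Randomisation and allocation concealment.** Minimisation uses GRIK1 genotype, OPRM1 genotype and antidepressant use.
- **Statistical analysis.** A medication-by-genotype mixed model names arm and genotype. In addition, "The topiramate medication group will also be separately analysed with genotype as the fixed effect (CC versus A carrier"). Further covariates are promised for sensitivity analyses, but none is named.
- **Psychological assessments.** Demographics are taken at baseline; whether they include ancestry is not stated.

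**The concern.** Within the topiramate arm, CC and A-carrier participants are compared as they come. If the CC frequency differs between ancestry groups, the two genotype groups differ in ancestry mix, and so in anything related to both ancestry and heavy drinking days. Stratified allocation does not remove this: it makes topiramate and naltrexone patients comparable within a genotype, not CC patients comparable with A carriers.

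The protocol's Background criticises the earlier retrospective evidence because its groups were not guaranteed to be alike at baseline, and the Discussion presents prospective work as protection against type 1 errors. The contrast for which GRIK1 power is claimed shares that weakness. Ancestry could create a genotype effect that is not there or hide one that is.

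**Working it through.** **1. The plan's own figure.** Inputs from Sample size calculations: "Power is considered for a two-sided test at α = 0.05 and a within-subject correlation of 0.35–0.40 for repeated measures"; 90 topiramate patients; CC about 42%. The moderate effect has no number, so d = 0.5 is assumed. Six weekly measures (weeks 7 to 12, the window stated for the primary comparison) are also assumed.

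- Groups: 90 × 0.42 = 37.8 CC and 52.2 A carriers.
- SD of a six-week mean, in units of the weekly SD: √[(1 + 5ρ)/6] = 0.707 at ρ = 0.40 and 0.677 at ρ = 0.35.
- Standard error at ρ = 0.40: 0.707 × √(1/37.8 + 1/52.2) = 0.151 SD.
- Power = Φ(0.5/SE − 1.96) = 91% at ρ = 0.40 and 93% at ρ = 0.35.

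The claim of more than 80% is reproduced under these assumptions. At d = 0.4 power would be 75 to 79%.

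**2. Does the European-only prevalence threaten power?** Hardly. At d = 0.5, six weeks and ρ = 0.40:

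| CC prevalence | Power |
|---|---|
| 42% | 91% |
| 30% or 70% | 87% |
| 20% or 80% | 77% |

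Power stays at or above 80% for CC between about 23% and 77%.

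**3. Ancestry imbalance between genotype groups.** The documents give no ancestry mix and no non-European frequency. Assume a non-European share w = 0.25, CC prevalence 0.42 in Europeans, and CC prevalence q = 0.15 or 0.70 in others.

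- Share non-European among CC = wq / [0.75 × 0.42 + wq].
- Share non-European among A carriers = w(1 − q) / [0.75 × 0.58 + w(1 − q)].
- q = 0.15: 0.0375/0.3525 = 0.106 against 0.2125/0.6475 = 0.328; gap 0.222.
- q = 0.70: 0.175/0.490 = 0.357 against 0.075/0.510 = 0.147; gap 0.210.

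**4. Spurious difference and type I error with no true genotype effect.** Assume the ancestry groups differ by D = 0.3 to 0.5 SD in weekly heavy drinking days. Bias = D × gap. Type I error = Φ(−1.96 + bias/SE) + Φ(−1.96 − bias/SE), with SE = 0.151.

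| q | D | Bias (SD, absolute) | Bias/SE | Type I error |
|---|---|---|---|---|
| 0.15 | 0.3 | 0.067 | 0.44 | 7.3% |
| 0.15 | 0.5 | 0.111 | 0.73 | 11.4% |
| 0.70 | 0.3 | 0.063 | 0.42 | 7.0% |
| 0.70 | 0.5 | 0.105 | 0.70 | 10.7% |

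Over a wider grid (w from 0.10 to 0.30, q from 0.10 to 0.85, same D, standard error recomputed at each mixed prevalence) the bias runs from 0.02 to 0.18 SD and the type I error from 5.3% to 23%.

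**5. The interaction model.** The test is (CC minus A carrier on topiramate) minus (CC minus A carrier on naltrexone). Drugs are randomised and balanced within GRIK1 genotype, so the expected ancestry gap is the same in both arms and an ancestry main effect cancels: D × gap − D × gap = 0. If the drug difference itself varies by M between ancestry groups, M × gap remains.

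**The case against.** The best counter-argument is that this is a condensed article. Covariates for secondary genotype models usually sit in the full protocol or analysis plan, the unnamed sensitivity covariates might include ancestry, and baseline demographics may already record it. Calling genotype the fixed effect names the exposure of interest; it need not be the complete model, and a repeated weekly outcome would normally carry time as well. The bias in the main scenario is also below one standard error of the contrast, and its direction is unknown.

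Much of this stands. It is fair to say only that genotype is the sole fixed effect named, and that ancestry may be collected already. It does not dispose of the point. The covariate sentence names nothing, is confined to sensitivity analyses and follows the drug comparison. The remark about accounting for sample differences belongs to the cost-effectiveness analysis. The non-randomised contrast is the one for which GRIK1 power is claimed, so its adjustment is more than routine detail.

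Three stronger readings are tempting but unsupported:

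- **That the European prevalence undermines the sample size.** Step 2 shows that power is insensitive to it.
- **That the allele and homozygote frequencies contradict each other.** Under Hardy-Weinberg, 0.65² = 42.25%, which lies inside the stated 41–43%, and the allele range is given as approximate.
- **That ancestry undermines the moderation test or the trial as a whole.** Step 5 shows that an ancestry main effect cancels in the interaction, and the topiramate versus naltrexone comparison is randomised.

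**Conclusion.** The concern holds for one analysis: the CC versus A-carrier comparison within the topiramate arm. As written, the plan leaves ancestry confounding open there, in a sample not restricted by ancestry and with a planning frequency that the protocol itself ties to one ancestry. The main illustration, 0.06 to 0.11 SD and a type I error of about 7 to 11%, rests wholly on assumed ancestry mix, frequencies and outcome shifts. It shows that a bias of consequence is possible; it does not demonstrate one. The primary comparison is unaffected, and the interaction is exposed only if response to the drugs differs by ancestry. The change is worth making because it is cheap, and because an ancestry adjustment chosen after genotype results are seen would bring back the post hoc problem that the trial sets out to avoid.

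**What to change.** Keep eligibility open. Then, before unblinding:

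- Record self-reported ancestry with the baseline demographics, if it is not already collected.
- Prespecify ancestry as a covariate in the topiramate-only genotype model.
- Add ancestry and medication-by-ancestry terms as a prespecified sensitivity analysis of the medication-by-rs2832407 model.
- Repeat the genotype analyses in participants of European descent, labelled as supportive only.

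**Cost.** At most one demographic item and a few lines of analysis-plan text, plus a small loss of precision from the extra terms. A European/other indicator leaves residual confounding if the other group mixes ancestries with different CC frequencies. The European-only repeat has less power: with 25% non-European, the topiramate arm falls from 90 to about 68, SE = 0.707 × √[1/(68 × 0.42) + 1/(68 × 0.58)] = 0.174 SD, and power at the assumed d = 0.5 is Φ(0.5/0.174 − 1.96), about 82% against 91%.

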### Statistical analysis

All available data from participants who took at least one dose of medication will be used, following the intention-to-treat principle. The primary outcome measure is frequency of HDDs (at least five standard drinks per day for men and at least four for women), which is a sensitive clinically relevant measure for alcohol trials [47]. Secondary outcomes (in addition to those listed above) will include number of abstinent days and average drinks per day. The two medication groups (naltrexone versus topiramate) will first be compared on weekly HDDs using mixed effects models followed by an analysis of secondary outcomes. Additional covariates will be included in the sensitivity analyses. Contrasts will also examine the final 6 weeks of the treatment period. Categorical variables will be compared using a chi-squared test. The medication by genotype groups will be compared using mixed models with fixed effects as intervention group (topiramate or naltrexone) and genotype (rs2832407*CC versus A carrier) as a moderating variable. The topiramate medication group will also be separately analysed with genotype as the fixed effect (CC versus A carrier). As with all alcohol treatment studies, we anticipate some participant dropout and intermittent missing data. Participants will be followed irrespective of whether they continue to receive treatment. Mixed effects models make use of all available responses under an assumption of ignorable missingness. The impact of missing data on the primary outcome measure will be explored by employing multiple imputation techniques and sensitivity analyses will be conducted to measure the effect of missing data on reported outcomes.

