### Randomisation and allocation concealment

The study is a double-blind, randomised trial with participants being randomised to receive one of two possible medication arms. The study is conducted under double-blind conditions so that participants and study staff are unaware of medication assignment. A computer-generated random allocation to topiramate or naltrexone is being provided by an independent service at the Clinical Trials Centre of the National Health and Medical Research Council (NHMRC) in Australia using minimisation stratified by *GRIK1* genotype, *OPRM1* genotype and the concurrent use of antidepressants. This is provided to the clinical trials pharmacist at each site for allocation to an intervention and dispensing medication. Researchers, clinicians and participants are all blinded to treatment allocation. In the event of a medical emergency that requires knowledge of the treatment condition in the opinion of the treating clinician at the time, the investigators can contact the 24-h telephone service at the NHMRC Clinical Trials Centre to break the randomisation code for that individual.

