### Psychological assessments

At baseline, demographics, medical history, personal and family history of AUD, and alcohol treatment history are obtained as in our previous trials [27–30]. Psychiatric diagnostic information is obtained with the MINI Neuropsychiatric interview [31]. The following measures are implemented at baseline and follow-up.Characteristics of alcohol dependence (baseline and follow-up):(i)Recent (last 30 days) alcohol consumption (frequency and quantity) assessed by the timeline follow-back method (TLFB) [32], with which we also measure tobacco use(ii)Severity of alcohol dependence assessed by the Alcohol Dependence Scale [33](iii)Craving for alcohol measured by the Penn Alcohol Craving Scale [34](iv)Drinker Inventory of Consequences (at baseline and at follow-ups) [35], which provides a measure of the social, physical and emotional consequences of alcohol use(v)Tension Reduction Alcohol Outcome Expectancies, which measures expectancies regarding the outcome of alcohol use [36].Mental health:(i)Depression, Anxiety and Stress Scale, which measures the severity of symptoms of depression, anxiety and stress [37](ii)Sleep problems assessed by the Insomnia Severity Index [38]Motivation and self-efficacy:(i)Stages of Change Readiness and Treatment Eagerness Scale (SOCRATES) assesses motivation to change [39](ii)Alcohol Abstinence Self-Efficacy (AASE) scale measures perceived self-efficacy [40]Cognitive and executive function:(i)The Montreal Cognitive Assessment (MoCA), which is used to screen for cognitive impairment that is likely to preclude the completion of study procedures and treatment [41](ii)Trail Making Test [42], which is used to screen for impairment and to measure the speed of processing and executive functioningPhysical health:(i)Health outcomes measured using the EQ-5D questionnaire [43] and Health and Performance Questionnaire (HPQ) [44]

We also collect daily drinking, medication usage and alcohol expectancies via SMS (automated email to SMS). Daily paper diaries supplement SMS where necessary. An assertive follow-up will be made to obtain data for all randomised participants, regardless of whether they drop out of the study.

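### Covariates are mentioned only for sensitivity analyses; the primary mixed model should name baseline heavy drinking days and the three minimisation factors

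*Protocol article*

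**What the plan says.** All references are to the protocol article.

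- **Statistical analysis.** The first comparison is naltrexone against topiramate on weekly HDDs by mixed effects models. No covariate is listed for it. The only sentence that assigns covariates to an analysis is "Additional covariates will be included in the sensitivity analyses". The moderation model lists medication group and GRIK1 genotype, and a separate model within the topiramate arm has genotype as its fixed effect. Baseline HDDs, OPRM1 genotype and antidepressant use are in no model described there.
- **Randomisation and allocation concealment.** Allocation is by minimisation on GRIK1 genotype, OPRM1 "genotype and the concurrent use of antidepressants".
- **Psychological assessments.** Drinking over the previous 30 days is measured by timeline follow-back (TLFB) at baseline and at follow-up.
- **Sample size calculations.** Power assumes a two-sided α of 0.05, "a within-subject correlation of 0.35–0.40 for repeated measures", and d = 0.33 "at week 7 that will persist through week 12", with 90 patients per arm. The claim is power above 80%. Nothing is said about the correlation between baseline and treatment values.

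**The concern.** Baseline HDD rate is likely to be one of the stronger predictors of HDDs on treatment, and it is not a minimisation factor. Adjustment in the model is therefore the way to keep a chance difference in baseline drinking out of the headline estimate. The Background itself faults the earlier pharmacogenetic result because comparable baseline characteristics were not guaranteed.

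The minimisation factors raise a related point. Balancing arms on prognostic factors and then leaving them out of the model gives a model-based standard error that is too large for the allocation used.

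At stake are the precision of the primary estimate, a confidence interval that matches the design, and a primary model fixed before the data are seen.

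**Working it through.** **Inputs from Sample size calculations:** d = 0.33, 90 per arm, two-sided α = 0.05, within-subject correlation ρ = 0.35–0.40, effect present in weeks 7–12 (m = 6 weekly values).

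**Assumptions added here:** compound symmetry, weekly SD set to 1, normal approximation, and a baseline-to-treatment correlation ρ_b, which the document does not give.

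**Step 1. Reproduce the plan's figure, with no covariate.**

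Variance of the six-week mean: V = (1 + 5ρ)/6.

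- ρ = 0.35: V = 2.75/6 = 0.4583
- ρ = 0.40: V = 3.00/6 = 0.5000

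Power = Φ(0.33/√(2V/90) − 1.96).

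- ρ = 0.35: 0.33/0.1009 = 3.270, power 90.5%
- ρ = 0.40: 0.33/0.1054 = 3.131, power 87.9%

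The claim of more than 80% is met without adjustment. A single week would give 60.0%, so the claim does rest on averaging over weeks.

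**Step 2. Adjust for baseline HDDs.**

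V_adj = V − ρ_b², so the share of variance removed is ρ_b²/V. First set ρ_b = ρ.

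- ρ = 0.35: 0.1225/0.4583 = 26.7%; V_adj = 0.3358; power 96.9%
- ρ = 0.40: 0.1600/0.5000 = 32.0%; V_adj = 0.3400; power 96.7%

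The standard error falls to √(0.3358/0.4583) = 0.856 and √(0.3400/0.5000) = 0.825 of its unadjusted value. The number per arm for 80% power falls from 67 to 49 and from 73 to 50.

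**Step 3. Vary the assumed baseline correlation (weeks 7–12 mean, 90 per arm).**

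| ρ_b | Variance removed, ρ = 0.35 | Variance removed, ρ = 0.40 | Adjusted power, ρ = 0.35 | Adjusted power, ρ = 0.40 |
|---|---|---|---|---|
| 0 (no adjustment) | 0% | 0% | 90.5% | 87.9% |
| 0.2 | 8.7% | 8.0% | 92.8% | 90.4% |
| 0.3 | 19.6% | 18.0% | 95.4% | 93.3% |
| equal to ρ | 26.7% | 32.0% | 96.9% | 96.7% |

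**Step 4. Vary the window, with ρ_b = ρ.** A single week gives ρ² = 12–16% removed. All 12 weeks give 30–36%.

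**Step 5. Loss of participants.** Dropout is expected but no rate is stated. Assuming a plain loss of 20% (72 per arm), unadjusted power is 83.3% (ρ = 0.35) or 80.0% (ρ = 0.40), and baseline-adjusted power is 92.7% or 92.4%. At 30% loss the figures are 78.1% or 74.5% unadjusted, and 89.2% or 88.8% adjusted.

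**Minimisation factors.** The document gives no prognostic effect for GRIK1, OPRM1 or antidepressant use on HDDs across both arms, so no gain from including them can be calculated.

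**The case against.** The strongest reply is that the article nowhere excludes baseline or the minimisation factors. The word *additional* could mean covariates beyond a core set that a condensed article does not list and that a full protocol or analysis plan would hold. Baseline might also enter the mixed model as one of the repeated measures. With baseline means constrained equal across arms, such a model recovers nearly all the precision of covariate adjustment.

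Part of this stands. A reader might infer that the primary model is known to ignore these variables, and the text does not establish that. But neither alternative is stated anywhere. They are also not equivalent: if baseline entered only through change scores, the variance would be V + 1 − 2ρ = 0.758 (ρ = 0.35) or 0.700 (ρ = 0.40), with power of 72–75%, against 88–90% ignoring baseline and about 97% with baseline as a covariate. If an unseen plan does adjust the primary model, the published sentence still needs to be reconciled with it.

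The second objection is that 27–32% depends on a borrowed correlation. This stands. The 0.35–0.40 is given for repeated measures in general. Entry requires an average of at least two HDDs per week, and withdrawal management may take place between screening and treatment. Both could make the baseline correlation lower. The calculation also treats a weekly count from 0 to 7 as normal, and it uses the final six weeks, which the analysis section describes as a further contrast.

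Third, omitting prognostic minimisation factors makes inference conservative rather than invalid, and GRIK1 is already a term in the moderation model. Both points are correct.

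**Conclusion.** The point holds as one of efficiency and clarity, and the change should be made. As worded, the plan names no covariate for its primary model and mentions covariates only for sensitivity analyses, although suitable variables are collected and three of them determine allocation.

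For baseline HDDs alone, adjustment would remove about 27–32% of the variance of the weeks 7–12 mean if the baseline correlation matches the plan's 0.35–0.40, about 18–20% at 0.3, and about 8–9% at 0.2. All of these assume compound symmetry.

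Three stronger readings are not supported:

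- **That the trial is underpowered or its sample size wrong.** The stated power is met without adjustment when loss is ignored. It reaches the 80% line or falls below it only under loss rates assumed here.
- **That 27–32% is an established loss, or that it includes the minimisation factors.** It is conditional and concerns baseline HDDs only.
- **That leaving out the minimisation factors invalidates the test.** If they are prognostic, the standard error is too large, which is conservative.

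**What to change.** In Statistical analysis, and in the analysis plan if one exists, replace the covariate sentence with a rule fixed before unblinding:

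- The primary mixed model includes as fixed effects baseline HDDs per week (from the 30-day TLFB), GRIK1 genotype (CC or A carrier), OPRM1 genotype (Asn40 homozygote or Asp40 carrier) and antidepressant use (yes or no).
- The unadjusted model and models with further covariates are sensitivity analyses.
- The medication-by-GRIK1 model, which already contains GRIK1, gains baseline HDDs, OPRM1 genotype and antidepressant use.

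If baseline is instead meant to be one of the repeated responses, say so and state that its mean is constrained equal across arms.

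The cost is a few lines of text. All the variables are already obtained before treatment starts, and the sample size need not change.
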